### Data collection

#### Characteristics of the participants

Participants’ age, sex, classification on the ACSF:SC [36], and the Abbreviated Sensory Profile 2 [37] will be collected after signing the informed consent and assent form.

#### Autism classification system of functioning: Social communication (ACSF: SC)

The ACSF:SC classifies the level of communication skills used by children with ASD [36]. Classification is divided into five levels that distinguish individuals’ social communication skills according to social needs and goals. The ACSF:SC was properly translated for Brazilian children and young people with ASD and will be applied by a trained assessor [38].

#### Sensory profile questionnaires

Sensory profiles of children in this study will be captured by the Abbreviated Sensory Profile 2. This questionnaire consists of 34 items which are answered by the caregiver and describes children’s responses to various sensory experiences [39]. Responses should consider how often (always, often, occasionally, rarely, never) the behaviors occur, and scores are given from 1 (always) to 5 (never). Lower scores indicate greater severity of sensory problems.

#### Outcomes

*Process and criteria for feasibility*. The process feasibility measures will include: Recruitment rates, number of patients who completed the study, as well as adherence, adverse events and satisfaction. Child’s adherence to the program will be evaluated through document analysis that will determine the number of children who started and completed the intervention. Interventionist reports on children’s behavior during the sessions and possible adverse events observed by them will also be documented. To analyze the general satisfaction of the participants, a semi-structured questionnaire adapted from Feitosa et al. [40] will be used (S1 File). This questionnaire will contain questions related to the format of the intervention, for example, satisfaction with the intervention schedule. This questionnaire also addresses the child’s interaction with the therapist, achievement of your prioritized goals. The completion of the questionnaire will be performed by the participants after the last day of the intervention.

The criteria or success for feasibility based on previous studies [41, 42] will include: ≥10% response rate from all eligible participants; and ≥80% of the participants successfully complete the study. (i.e. completed baseline, immediate and post follow up). Given the nature of the other feasibility measures they will not have cut-off criteria to determine the feasibility of performing a complete RCT. Instead, their results will be reported descriptively and will be used to determine the suitability of a full RCT combined with the others specific criteria mentioned.

This protocol study will follow one of the recommendations: not feasible, feasible with minor modifications, or feasible with closing monitoring [33].

Scientific feasibility. Preferred sports-related activity and physical activity participation goals

Activity and physical activity participation goals will be evaluated by the Goal Attainment Scaling–GAS [43, 44]. GAS is patient centred and has been widely used to quantify the achievement or fulfillment of goals previously defined in an intervention program [43–46]. In this study, goals will be selected by caregivers. In order to increase responsiveness, validity and reliability, three goals that can be affected by the treatment will be identified [47]. The first refers to performance of a sport-related motor activity, the second and third refers to attendance and involvement in leisure-time physical activities during sports or physical recreation participation (see example in Table 1). All GAS’ will be shared among caregivers and interventionists at baseline by another non-blinded assessor.

**Table 1 pone.0291488.t001:** Goal attainment scale examples.

Score	Meaning	Sports-related activity example	Attendance of physical activity participation	Involvement of physical activity participation
		*Parent’s goal*: *To dribble a soccer ball with control along the soccer field*	*Parent’s goal*: *To participate in soccer classes at least twice in a week*	*Parent’s goal*: *To be engaged at least 30 minutes when participates in school’s sports activities of one-hour duration*
**-2**	Current level	Dribbles a soccer ball during 4 meters of the soccer field without lose control of the ball	Does not participate in soccer classes in a week	Is not engaged at all during school’s sports activities
**-1**	Less than expected	Dribbles a soccer ball during 6 meters of the soccer field without lose control of the ball	Participate in soccer classes one day in a week	Is engaged in 15 minutes during school’s sports activities
**0**	Expected to achieve	Dribbles a soccer ball during 10 meters of the soccer field without lose control of the ball	Participate in soccer classes two days in a week	Is engaged in 30 minutes during school’s sports activities
**+1**	More than expected	Dribbles a soccer ball during 12 meters of the soccer field without lose control of the ball	Participate in soccer classes three days in a week	Is engaged in 45 minutes during school’s sports activities
**+2**	Much more than expected	Dribbles a soccer ball during 14 meters of the soccer field without lose control of the ball	Participate in soccer classes four days in a week	Is engaged in 60 minutes during school’s sports activities

*Activity Competence and sense of self*

***Ignite Challenge*:** Measures accuracy and speed of locomotor and object control skills necessary for sports and active recreation activities [48]. It is a 13-item measure that can be used in children with ASD classified at ACSF levels I and II. The instrument total raw score is converted in percentage points. The higher the score, the better the performance. It can include “picture cards” for each test item to supplement evaluators’ demonstrations and improve understanding of each test item [49–51]. The *Ignite Challenge* has demonstrated excellent inter-rater (ICC = 0.91 (95% = 0.93, 0.99), intra-rater (ICC = 0.96, 95% = 0.90, 0.98) and rest-test (ICC = 0.91, 95% = 0.84, 0.95) reliability in Australian children with ASD (n = 47) [51].**Test of Gross Motor Development-2—TGMD-2:** Is used in children up three to 10 years, it assesses accuracy and quality of 12 fundamental motor skills, six of which are locomotor skills and six are object control skills. The total scores of each subtest are summed and represented as raw scores, which can be converted into motor quotients [52]. The TGMD-2 was validated and reliable for typical Brazilian children in the study by Valentini et al. [53] and has been used in children with ASD [54, 55]. Furthermore, it has been seen as a responsive measure in the Australian Sports Stars in children with CP [18]. Reliability of the TGMD-2 for children with ASD is currently being evaluated by our research group (ongoing study).**10×5 Sprint Test–(10×5ST) and Muscle Power Sprint Test (MPST):** The 10×5ST assesses agility [56, 57]. In the 10×5ST, participants need to run 5 m separated by 2 cones, 10 times continuously, making turns in the cones that mark the end of the five meters [57]. The 10×5ST has excellent inter-observer and test-retest reliability (ICC = 1.00 and 0.97) and good reported construction validity. An increase in agility of 3.2 seconds is considered a real change [54]. Participants muscle power will be evaluated by the Muscle Power Sprint Test–MPST [54]. The MPST measures muscle power by asking the participant to run as fast as possible for 15 m, 6 times, with a 10 second interval between each sprint. The MPST has high inter-observer and test-retest reliability (ICC = 0.97 and 0.99) for ambulant children with CP [56]. Reliability of the MPST and 10x5ST for children with ASD is currently being evaluated by our research group (ongoing study).**Pediatric Evaluation of Disability Inventory—Computer Adaptive—PEDI-CAT ASD:** Will be used to assess the domains of mobility (activity competence) and sense of self (responsibility) [58]. In the PEDI-CAT domain mobility the four-point scores are based on different levels of difficulty. The responsibility domain ranks items on a five-point scale, describing the division of responsibility between the caregiver and the child in managing complex, multi-step life tasks. The PEDI-CAT was adapted and presented reliability to be used by children with autism [59]. It was translated and culturally adapted for the Brazilian population aged 0–21 years [60].**Physical Literacy Profile Questionnaire–PLPQ:** Assesses the components of physical literacy (physical, cognitive, social and psychological) of children [61]. The questions are related to performance and satisfaction in the physical, social, psychological and cognitive competencies. Each item assesses performance on a scale of 0 to 2 and each item assesses the child/adolescent/young adult’s performance satisfaction on a scale of 1–10 points. The higher the score, the higher the level of performance and satisfaction. The QPAF is in the process of being validated by our research group, preliminary data showed good test-retest reliability for children with CP (ICC = 0.84; IC [95%]: 0.74–0.91) (data not published yet) [61].
*Overall Participation at home, school and community*
**Participation and Environment Measure for Children and Youth—PEM-CY:** Will be used to assess participation at home, school and community [62, 63]. The measure identifies attendance and involvement of children in activities carried out at home, at school and in the community, as well as the characteristics of these environments that influence participation in six parts: frequency of participation, involvement of participation, desire to change participation, support for the environment, support for the environment and environmental resources [64, 65]. The PEM-CY has moderate to good internal consistency and test-retest reliability indices [62] and was translated and culturally adapted for the Brazilian population [58]. The PEM-CY it has been used as an outcome measure to assess the effects of participation interventions on individuals with ASD [66, 67].

*Randomization and blinding*. Children (n = 38) will be randomized into 2 groups (Sports Stars Brazil intervention and control group). Randomization will occur when 8 to 10 the child has been recruited and the allocation ratio will be 1:1. The randomization will be performed using a computer-generated random sequence to ensure equal allocation to each group. This sequence will be used to randomize children into the immediate group, or the control group. A new sequence will be used for each subgroup randomization until 36 children are allocated, or no further participants can be recruited. All assessments will be performed before the allocation of each subgroup. Thus, the use of the block randomization method is unlikely to increase the probability of identifying the allocation of participants.

An independent researcher, not involved in recruitment or data collection and without direct contact with those involved in this research, will perform all randomization steps. The randomization process and allocation of participants will be supervised by the independent investigator. Due to the intervention characteristics of this study, it is not possible to blind participants and interventional therapists to group allocation. In order to minimize bias, the children and their caregivers will be instructed to not tell the assessors which group they are in until after all their baseline assessments were completed. Furthermore, all the two blinded assessors will be asked to indicate if they know which group (control or intervention, and if so to cite the source of unblinding). This will permit to report the success of blinding. The statistician will be blinded to the group allocation until the completion of the analyses.

The possible contamination of information between the groups will also be evaluated. For this, the following questions will be asked. 1) Have you talked to other participants in this study about the intervention they are receiving? 2) If so, did your attitude towards the intervention change after talking to one of the participants in the other group? 3) Did you have any changes related to physical activity after the first contact with our project? 4)Are any of the participants in the other group aware of the type of intervention you were receiving in this study?

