**Methods:**

This study will be conducted with 36 participants with ASD aged 6 to 12 years old following the CONSORT for pilot and feasibility recommendation. Participants will be randomly allocated into two groups. Intervention group will receive eight, weekly Sports Stars sessions. Each session will include of sports-focused gross motor activity training, confidence building, sports-education and teamwork development. Study assessments will occur at baseline, immediately post-intervention and 20-weeks post-randomization. First, we will assess process feasibility measures: recruitment, assessment completion, adherence, adverse events and satisfaction. Second, we will investigate the scientific feasibility of the intervention by estimating the effect size and variance at the level of achievement sports-related activity and physical activity participation goals (Goal Attainment Scaling), activity competence (Ignite Challenge, Test of Gross Motor Development-second edition, Physical Literacy Profile Questionnaire, Pediatric Disability Assessment Inventory–Computer Adaptive Test—PEDI-CAT—mobility, 10×5 Sprint Test and Muscle Power Sprint Test), sense of self (PEDI-CAT—responsibility), and overall participation at home, school and community, (Participation and Environment Measure for children and young people, PEM-CY).

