### Procedures

Children with ASD will be recruited through advertisement, radio spots, social media networks, as well as recruited by convenience from public or philanthropic institutions and private rehabilitation clinics in Belo Horizonte, Brazil. All eligible individuals will receive clarifications regarding the objectives of the study and will sign a statement of informed consent prior to participation. Participants characteristics will be collected. Finally, two blinded researchers will collect the outcome data at baseline, 8 weeks after randomization, and the follow-up evaluation. All assessments will be repeated by the same assessors.

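### Families are asked to conceal their group only until baseline is complete, before any group has been assigned, so the instruction protects neither post-randomisation assessment.

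*Protocol article*

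**What the plan says.** The Randomization and blinding text (under Outcomes) accepts that "it is not possible to blind participants and interventional therapists to group allocation". To limit the resulting bias, it says that children and caregivers "will be instructed to not tell the assessors which group they are in until after all their baseline assessments were completed".

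The same text fixes the order of events: "All assessments will be performed before the allocation of each subgroup". The Procedures section says that "two blinded researchers will collect the outcome data at baseline, 8 weeks after randomization, and the follow-up evaluation", and adds: "All assessments will be repeated by the same assessors". The Methods part of the abstract gives the timetable: "Study assessments will occur at baseline, immediately post-intervention and 20-weeks post-randomization".

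Two other blinding measures are stated. For the assessors, "all the two blinded assessors will be asked to indicate if they know which group", and they are to name the source if they do. For the analysis, "The statistician will be blinded to the group allocation until the completion of the analyses".

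**The concern.** A request to keep the allocation secret is useful only from the moment an allocation exists until the last outcome has been scored. The request in the protocol runs over the opposite period: it ends with baseline, and allocation comes after baseline. Followed as written, it asks nothing of families at either visit where their group could influence an assessor.

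The trial's scientific aim is at stake. The plan forgoes significance tests and sets out to estimate effect size and variance for a definitive RCT. Scoring by assessors who know the group could shift those estimates, and leaving out p-values gives no protection against that. The planned report on the success of blinding would also lose value. If unblinding were found, one could not tell whether assessor blinding is unachievable in this setting or simply was not asked for.

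**Working it through.** No calculation is needed to test the point, and the plan gives no figure to reproduce. The check is one of sequence.

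**Order of events and cover given by the instruction**

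| Step | Source | Does a group exist to disclose? | Is the instruction in force? |
|---|---|---|---|
| Baseline assessment | Procedures; Randomization and blinding | No | Yes |
| Allocation of the subgroup | Randomization and blinding | Created here | Already ended |
| 8 weeks after randomisation | Procedures | Yes | No |
| 20 weeks after randomisation | Abstract, Methods | Yes | No |

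The sentence placing all assessments before allocation must mean the baseline assessments, because the later visits are timed from randomisation and cannot precede it. On that reading the instruction covers 1 of 3 visits, and that one is the visit where it does nothing. It covers 0 of the 2 post-randomisation visits.

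**Does another measure fill the gap?**

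- The question to assessors about whether they know the group records unblinding and its source. It does not prevent it.
- The independent researcher who runs the randomisation keeps the assessors out of allocation, but has no bearing on what a family says at a visit.
- Blinding the statistician protects the analysis, not the scoring.
- The separate non-blinded assessor who shares the GAS goals is mentioned for baseline only.
- The contamination questions concern talk between participants, not talk with assessors.

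The instruction is therefore the only stated measure against disclosure by families to assessors.

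**Which outcomes are exposed?**

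The nine scientific-feasibility outcomes are GAS, Ignite Challenge, TGMD-2, 10×5 Sprint Test, Muscle Power Sprint Test, PEDI-CAT mobility, PEDI-CAT responsibility, the Physical Literacy Profile Questionnaire and PEM-CY. At least four of the nine are tests run or scored by the assessor: Ignite Challenge, TGMD-2 and the two sprint tests.

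**How disclosure reaches the estimate**

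The Data analysis text defines the effect size as

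*d* = (mean change, treatment − mean change, control) / pooled SD.

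Each change is a post-randomisation score minus a baseline score. If knowledge of the group moved post-randomisation scoring by *b* units in one group relative to the other, then, with the pooled SD held fixed, *d* would move by *b* / pooled SD. The document gives neither *b* nor the SDs, so no size can be put on this. Because the same assessors repeat all assessments, a disclosure at 8 weeks also carries over to 20 weeks.

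**The case against.** The strongest reply is that this is a slip of the pen. The Procedures section calls the assessors blinded at all three time points, and asking assessors what they know makes little sense if disclosure were permitted. The word baseline may have been written where the later visits were meant, and the text nowhere says that families may tell. That is plausible. But no other sentence gives the intended end point, and staff preparing family instructions from this text would use the wrong one.

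A second reply is that the exposure is uneven. The article reports inter-observer ICCs of 1.00 for the 10×5 Sprint Test and 0.97 for the Muscle Power Sprint Test, so timed runs leave less room for biased scoring than the movement-quality ratings of TGMD-2. This stands as a matter of degree. Encouragement during a sprint could still differ by group, the Muscle Power Sprint Test figure is for children with cerebral palsy, and reliability in ASD is still under study. If the questionnaires are answered by families, as seems likely, they come from unblinded respondents in any case and a longer instruction would not change that.

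A third reply is that this is an open pilot whose two numerical success criteria (at least 10% response, at least 80% completion) do not depend on blinding. That is correct, and the process-feasibility conclusions are not threatened. The effect sizes are a separate stated aim, and they are what is exposed.

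**Conclusion.** The concern holds. As written, the instruction fails its stated purpose: it is in force only while there is nothing to conceal, and it lapses before both visits that supply the post-randomisation scores. It conflicts with the description of the assessors as blinded at those visits, and nothing else in the document repairs it.

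Its extent is 0 of 2 post-randomisation visits protected, with at least four of nine outcomes depending on the assessor and TGMD-2 quality ratings probably the most exposed. The conclusion rests on one reading, that the assessments placed before allocation are the baseline ones, which is the only workable reading. It does not assume that unblinding will occur, only that the plan leaves the way open. The bias could be small or material; the document does not allow an estimate.

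**What to change.** In the Randomization and blinding text, replace the end point of the instruction (completion of the baseline assessments) with *until after the 20-week follow-up assessment is completed*. State that families receive the instruction at allocation and are reminded before the 8-week and 20-week visits. Ask the assessors whether they know the group, and how they learned it, straight after each of those two visits, so that the report on blinding refers to the visits where blinding matters. While editing, insert *baseline* in the sentence that places all assessments before allocation.

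The essential change is one sentence in the protocol and the matching wording in the family instructions. The reminders and the timing of the assessor question are small operational additions. No extra staff or visits are needed. The correction should be in place before the first 8-week visit, because blinding lost at a visit cannot be restored.

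### The assessor blinding check records only declared knowledge of the group, and the instruction to families not to disclose lapses at baseline, before any group exists

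*Protocol article*

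**What the plan says.** All references are to the protocol article.

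- **Procedures.** Outcome data are collected by blinded researchers at three visits: "two blinded researchers will collect the outcome data at baseline, 8 weeks after randomization, and the follow-up evaluation". The abstract dates the last of these: "Study assessments will occur at baseline, immediately post-intervention and 20-weeks post-randomization".
- **Randomization and blinding (under Outcomes), instruction to families.** Children and caregivers are "instructed to not tell the assessors which group they are in until after all their baseline assessments were completed".
- **Same section, the check.** The article states that "blinded assessors will be asked to indicate if they know which group (control or intervention, and if so to cite the source of unblinding". The stated purpose follows: "This will permit to report the success of blinding".
- **Same section, order of events.** Each subgroup of 8 to 10 children is assessed before it is allocated. Participants and therapists cannot be blinded.

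The article mentions no guess from an assessor who does not claim to know the group, no rating of certainty, and no time at which the question is put.

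**The concern.** Two gaps sit next to each other.

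First, the item and the conclusion drawn from it do not match. An assessor who was told nothing, but correctly suspects the arm from a child's remark or behaviour, can truthfully say they do not know. That child is then counted as blindly assessed.

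Second, the instruction not to disclose is tied to the one visit where there is nothing to disclose. The visits at which unblinding could bias a rating are those at 8 and 20 weeks.

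Participants and therapists are unblinded, so assessor blinding is the main protection for the tests an examiner scores. Ignite Challenge scores accuracy as well as speed, and TGMD-2 scores the quality of movement, so both leave room for judgement. Their effect sizes and variances are part of the scientific-feasibility output meant to inform a full trial. Disclosure is plausible: intervention children train in groups of four or five drawn from small waves that the same assessors examined at baseline.

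**Working it through.** The article gives no figure for the blinding check, so there is none to reproduce. The check has three steps.

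**1. Timeline against the instruction.** The final visit is 8 + 12 = 20 weeks after randomisation (12 weeks post intervention, Statistical methods), which agrees with the abstract.

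| Event | Group exists? | Covered by the instruction as worded? |
|---|---|---|
| Baseline assessment | No | Yes |
| Allocation of the subgroup | Assigned here | – |
| 8-week assessment | Yes | No |
| 20-week assessment | Yes | No |

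**2. What the item can identify.** Take N = 36 (Sample size rationale; the randomisation text also gives 38 once, which does not affect the argument). Let k be the number of children whose group the assessor declares known, and assume all k are correct. The item yields k/36. If every assessor had to guess for every child, the share correct would be at least k/36 and at most 1. If the remaining guesses were at chance it would be (k + (36 − k)/2)/36. The values of k are illustrations.

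| k | Declared known, k/36 (exact 95% CI) | Correct if the rest are at chance | Possible range of correct guesses |
|---|---|---|---|
| 0 | 0% (0 to 10%) | 50% | 0 to 100% |
| 4 | 11% (3 to 26%) | 56% | 11 to 100% |
| 9 | 25% (12 to 42%) | 63% | 25 to 100% |
| 18 | 50% (33 to 67%) | 75% | 50 to 100% |

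The confidence interval describes declared knowledge only. It says nothing about the last column, where suspicion would appear.

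**3. What a recorded guess would add, and how precisely.** Within an arm of n children, the Bang index is (correct − incorrect)/n, with cannot-say answers counted in n. If nobody answers cannot say, this is 2p − 1, where p is the share correct, with standard error 2√(p(1 − p)/n). For an assumed p = 0.70 and n = 18:

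- index = 2 × 0.70 − 1 = 0.40;
- standard error = 2√(0.21/18) = 0.216;
- 95% half-width = 1.96 × 0.216 = 0.42, so the interval runs from −0.02 to 0.82.

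This treats the guesses as independent. Two assessors make them all, and guesses within a wave are linked, so the real uncertainty is probably larger.

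**The case against.** The strongest reply is that the check does produce something reportable: how many allocations the assessors say they know, and how they learned them. The parenthesis in the question may even mean that the assessor names the group. A guess has its own weakness, because a correct guess may reflect a visible treatment effect rather than a leak. The article may leave the form's wording and timing to the full protocol. This is also an open pilot without significance tests, and assessor blinding is not among its listed process-feasibility measures.

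Most of this stands and limits the size of the point. It does not remove it. The article itself states that the item permits the success of blinding to be reported, and that does not follow from declared knowledge alone. The wording about families is explicit, whatever the full protocol adds. It may be a slip for all assessments rather than baseline ones, but it should then be corrected.

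A reader might infer more than the text supports:

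- **That blinding cannot be reported at all.** It can, as declared unblinding with its source.
- **That a known-unblinded assessor stays with the child to week 20.** Procedures does say "All assessments will be repeated by the same assessors", but this is a general consistency rule. No sentence addresses an unblinded assessor, and any carry-over depends on when the question is asked.
- **That the statement on block randomisation is wrong.** The article says that "the use of the block randomization method is unlikely to increase the probability of identifying the allocation of participants", but draws this from assessments preceding allocation. It is already confined to baseline.
- **That one remark unblinds a whole wave.** That is a worst case, in which a child names every team-mate.

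**Conclusion.** The point holds in a limited form. The planned question measures declared unblinding and its source. It does not measure suspicion, so the claim that it shows the success of blinding goes further than the item allows. Separately, the instruction to families, read literally, expires before allocation and protects neither post-randomisation visit.

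The size of any resulting bias cannot be derived from the document. What can be said is that a declared share of k/36 leaves the share of correct guesses bounded only between k/36 and 100%. This assumes 36 children and that every declared allocation is correct. The practical consequence is confined mainly to the examiner-scored tests and to what the pilot can tell a later trial about keeping assessors blind. It is a modest defect, worth correcting because the correction is nearly free.

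**What to change.** In Randomization and blinding:

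1. After each post-randomisation visit, and for each child, the assessor records a guess (Sports Stars, control, cannot say), the reason for it, and whether the group was disclosed and by whom.
2. Report declared unblinding and correct guesses by arm and visit, descriptively. The Bang index with a 95% CI would serve, with a note that guesses within a wave and from only two assessors are not independent.
3. Extend the instruction not to disclose the group through the 20-week assessment.

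The cost is one form line per child per visit and no extra staff. The drawbacks are wide intervals (about ±0.42 per arm in the example above) and guesses that may partly reflect a visible treatment effect, which the recorded reason helps to separate.

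I would not add a rule moving children to the other assessor after unblinding. It changes the rater mid-series, probably more often in one arm, while TGMD-2 reliability in ASD is still being evaluated. Nothing in the article shows that the second assessor would be free or still blind. The block-randomisation sentence needs no change.
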